**Discussion::**

The primary endpoint will be tested with a 2-sample *t* test, or a Wilcoxon rank sum test. Any other continuous variables will be tested via an analysis of covariance, while categorical variables will be tested by a Chi-squared or Fisher exact test. Repeated measure analysis of variance will be performed to explore any in-group differences. The results will be addressed with a 95% confidence interval. We expect that MBBG will be the 1st TKM-based mobile application to be feasible for primary care in subhealth management.

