#### Subhealth awareness

2.7.1

The primary outcome is the awareness of subhealth status. The participants will be given a questionnaire, consisting of 4 items: “Have you known or heard of subhealth statuses?” “Do you think that preventing diseases is as important as treating them?” “Do you think a professional medical service aimed at managing subhealth statuses is necessary?” “Are you willing to use a professional medical service to manage subhealth status, if available?” Each item is then scored from 1 (Not at all) to 7 (Absolutely), with the total score falling in the range of 4 to 28 points. The higher the score, the higher the awareness level. All participants are supposed to submit the subhealth awareness questionnaire during every visit (visits 1, 2, and 3) either via the mobile application or in a classic face-to-face fashion.

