### Hypothesis and sample size calculation

2.8

The primary objective of this study is to compare the awareness levels of subhealth statuses between the MBBG and control groups. The null hypothesis is that there is no difference between the awareness score means between the groups. Since there have not been any previous studies implementing the MBBG application, we adopted another clinical trial to explore the mental health benefits of a mobile application. They addressed a 0.58 effect size with a 6-week test.^[8]^ This study set the intervention period as 12 weeks, and the age for the inclusion criteria is higher, and so we assumed the effect size to be, conservatively, 0.5. Therefore, the sample size has been calculated as 60 per group (2-sided, *α* = 0.05 and 1 − *β* = 0.8, independent *t* test) with G∗ power software version 3.1.3.^[17]^ With a 20% dropout rate expected, we will enroll 150 participants (75 in each group) to account for this.

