### Statistical analysis

2.9

The full analysis set is defined as a group including participants who are allocated to either the intervention or control group, use the MBBG application at least once, and assesses the primary outcome at least once. Per protocol set is defined as a group of the included participants who follow the trial procedure and demonstrate at least 70% compliance. The study results are analyzed primarily with the full analysis set, and subordinately with the per protocol set.

The primary variable in question is the difference in the subhealth status awareness levels between the baseline (visit 1) and the endpoint (visit 3). The mean difference will be tested using a 2-sample *t* test, or a Wilcoxon rank sum test. Any other continuous variables between the baseline and visits 2 or 3 will be tested independently, by an analysis of covariance with a covariate of the baseline values, while categorical variables will be tested by a Chi-squared or Fisher exact test. Repeated measure analysis of variance will be performed to explore any in-group differences between each of the variables throughout all visits. All of the results, analyzed with R software version 3.5.2 or later, will be addressed at a 95% confidence interval.

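### The primary awareness outcome is tested as an unadjusted change score although its baseline is collected and ANCOVA is planned for the other continuous outcomes; the test is valid but less precise

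*Protocol article*

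**What the plan says.** Section 2.9 (Statistical analysis) of the protocol article defines the primary variable: "The primary variable in question is the difference in the subhealth status awareness levels between the baseline (visit 1) and the endpoint (visit 3". The test follows: "The mean difference will be tested using a 2-sample *t* test, or a Wilcoxon rank sum test". No covariate is named. The next sentence has the remaining continuous variables analysed "by an analysis of covariance with a covariate of the baseline values". The abstract draws the same line: the primary endpoint gets the t or Wilcoxon test, then "Any other continuous variables will be tested via an analysis of covariance". No reason is given for treating the primary outcome differently.

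Section 2.7.1 (Subhealth awareness) shows that the covariate will exist: "All participants are supposed to submit the subhealth awareness questionnaire during every visit (visits 1, 2, and 3". The score is a sum of four items, "with the total score falling in the range of 4 to 28 points".

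Section 2.8 (Hypothesis and sample size calculation) states the null hypothesis on scores, not changes: "The null hypothesis is that there is no difference between the awareness score means between the groups". For the effect size, "we assumed the effect size to be, conservatively, 0.5". It does not say whether that 0.5 is in SDs of the score or of the change. The calculation is for an independent t test, two-sided 5% level, 80% power, giving 60 per group and 75 per group after 20% dropout.

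**The concern.** Subtracting the baseline fixes the slope of the visit 3 score on the visit 1 score at 1. ANCOVA estimates that slope. Unless the two scores are almost perfectly correlated, the slope is below 1 (with equal SDs it equals the correlation), so the change score over-corrects and carries avoidable noise from visit 1.

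The plan therefore uses the less precise of its two methods on the outcome for which the trial was sized. Precision matters here because the sample size has no reserve: it was set for exactly 60 evaluable participants per group. A wider confidence interval and a higher chance of missing a real effect are at stake. The validity of the test is not.

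**Working it through.** **Inputs.** From section 2.8: effect size 0.5, two-sided 5% level, 80% power, 60 evaluable per group (75 × 0.8 = 60). Assumed, because the document does not give them: equal SD s at visits 1 and 3, and a visit 1 to visit 3 correlation r between 0.3 and 0.7, with 0.9 as a high case.

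**The plan's own figure.** For d = 0.5 the normal approximation gives 63 per group and the exact (noncentral t) calculation gives 64, not 60. Exact power at 60 per group is 77.5%. This small shortfall comes from the sample size and is present with or without a covariate.

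**Variances.**
- Change score: 2s²(1 − r).
- ANCOVA residual: s²(1 − r²).
- Ratio, ANCOVA to change: (1 − r²) / [2(1 − r)] = (1 + r)/2.

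The ratio is below 1 for every r below 1, so the direction does not depend on the assumed r. It is 0.65, 0.75, 0.85 and 0.95 at r = 0.3, 0.5, 0.7 and 0.9, a variance saving of 35%, 25%, 15% and 5%.

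**Power at 60 per group, effect of 0.5 in SDs of change.** The planned test has d = 0.5. ANCOVA has an effective d of 0.5 × √[2/(1 + r)].

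| r | planned test | ANCOVA d | ANCOVA power | n per group for 80% with ANCOVA |
|---|---|---|---|---|
| 0.3 | 77.5% | 0.620 | 92.1% | 42 |
| 0.5 | 77.5% | 0.577 | 88.0% | 49 |
| 0.7 | 77.5% | 0.542 | 83.8% | 55 |
| 0.9 | 77.5% | 0.513 | 79.6% | 61 |

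**Power at 60 per group, effect of 0.5 in SDs of the score.** The planned test has an effective d of 0.5/√[2(1 − r)]; ANCOVA has 0.5/√(1 − r²).

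| r | planned d | planned power | ANCOVA d | ANCOVA power |
|---|---|---|---|---|
| 0.3 | 0.423 | 63.1% | 0.524 | 81.3% |
| 0.5 | 0.500 | 77.5% | 0.577 | 88.0% |
| 0.7 | 0.645 | 93.9% | 0.700 | 96.7% |

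The ANCOVA figures ignore the one degree of freedom spent on the covariate, which is negligible with 120 participants.

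**Chance baseline imbalance is not an additional loss.** The SD of the baseline mean difference is √(2/60) = 0.183 score SD. At r = 0.5 an imbalance of that size moves the change-score estimate, relative to ANCOVA, by (1 − 0.5) × 0.183 = 0.091 SD. The variances of the two estimates at r = 0.5, in units of s², are 2/60 = 0.0333 (change) and 0.75 × 2/60 = 0.0250 (ANCOVA). Their difference is 0.0083, and its square root is 0.091. The shift is the same precision loss in other units.

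**The case against.** The strongest defence is that nothing here is an error. Under 1:1 randomization an unadjusted comparison of changes keeps its type I error and is unbiased, and it matches the independent t test used for planning. Using different methods for primary and secondary outcomes is not a contradiction. All of this stands, and it makes the point one of efficiency.

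Three stronger readings are tempting and are not supported:
- **The estimate is biased towards the arm that starts lower.** This is true only given a particular chance imbalance. It averages to zero over randomizations, and its cost is already in the variance ratio.
- **Power falls well short of 80% whenever r is below 0.5, if the 0.5 is in SDs of the score.** Near r = 0.5 it does not: power is 76.7% at r = 0.49 and 73.6% at r = 0.45. The deficit is large only for clearly lower r (63% at 0.3), and above about r = 0.53 the planned test reaches 80%.
- **The 77.5% is caused by the missing covariate.** With the effect in SDs of change, it arises because 60 is fewer than the 64 that an exact t test needs.

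It is also fair to say that the size of the gain is unknown. Neither r nor any SD is given, and at r = 0.9 the saving is only 5%. Finally, the Wilcoxon option may reflect concern about a short, bounded score, so a switch to ANCOVA should not discard it without a replacement.

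**Conclusion.** The point holds as a recommended gain in precision. The primary test is valid but uses less of the available information than the method the same section applies to the other continuous outcomes. The direction is certain for any r below 1 with equal SDs. The size is not: a variance saving of 35% to 15% over the assumed range r = 0.3 to 0.7, falling to 5% at r = 0.9. Over r = 0.3 to 0.7, ANCOVA gives more than 80% power at 60 per group on either reading of the effect size. The planned test stays at 77.5% on one reading and runs from 63% to 94% on the other. Section 2.8 does not say which reading was meant.

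**What to change.** In section 2.9, make the primary analysis an ANCOVA of the visit 3 awareness score on group, with the visit 1 score as covariate. Report the adjusted mean difference with its 95% confidence interval. Using the change as the response with the same covariate gives the same group effect, so the stated interest in change is kept. Retain the t/Wilcoxon comparison of change, or a rank-based ANCOVA, as a sensitivity analysis. Align the abstract.

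Because the trial is open-label, register the change before any outcome data are examined by group, so that the choice of adjustment cannot follow the results. Section 2 already provides for amendments to be reflected in the registry.

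The cost is one degree of freedom and a registered amendment. No additional data or participants are needed.

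### The primary awareness endpoint is left without the baseline adjustment that the other continuous outcomes receive, which generally costs precision

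*Protocol article*

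**What the plan says.** Section 2.9 (Statistical analysis) defines the endpoint as a change score: "The primary variable in question is the difference in the subhealth status awareness levels between the baseline (visit 1) and the endpoint (visit 3"). It then names the test: "The mean difference will be tested using a 2-sample *t* test, or a Wilcoxon rank sum test". No covariate is mentioned. The next sentence treats the remaining continuous variables differently; they are to be "tested independently, by an analysis of covariance with a covariate of the baseline values". The Discussion paragraph of the abstract makes the same division, giving the t test or Wilcoxon test to the primary endpoint and then stating: "Any other continuous variables will be tested via an analysis of covariance".

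The covariate is available. Section 2.7.1 says: "All participants are supposed to submit the subhealth awareness questionnaire during every visit (visits 1, 2, and 3"). Section 2.8 puts the hypothesis in terms of means: "The null hypothesis is that there is no difference between the awareness score means between the groups". The trial is sized on an independent t test, and on the effect size section 2.8 says: "we assumed the effect size to be, conservatively, 0.5". It does not say whether that 0.5 is in SDs of the raw score or of the change.

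**The concern.** The article gives no reason why the primary endpoint alone should go without the adjustment used for the other continuous outcomes. A change score subtracts the whole baseline value, which amounts to fixing the slope on baseline at 1. ANCOVA estimates that slope. When the slope is below 1, subtracting the whole baseline adds noise that ANCOVA removes. The least efficient of the planned between-group methods for continuous data may therefore fall on the comparison that carries the trial's conclusion. What is at stake is power and the width of the primary confidence interval, not the validity of the result.

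The rank sum alternative fits section 2.8 less well than a comparison of means does. Without an assumption of a pure location shift, it does not test a null hypothesis about means.

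**Working it through.** **Inputs from the article.** Effect size 0.5, two-sided alpha 0.05, power 80%, independent t test, 60 per group before dropout, 20% dropout, 75 per group enrolled (all section 2.8).

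**Assumptions.** The correlation r between baseline and week-12 awareness is not given and is shown as a range. The SDs at baseline (s0) and week 12 (s1) are taken as equal at first.

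**The plan's own figure.** The exact noncentral t calculation at effect size 0.5 gives 63.77, so 64 per group, not 60. The normal approximation gives 63. At 60 per group the exact power is 77.5%. The dropout step does reproduce: 60/(1 − 0.20) = 75. The gap between 60 and 64 is a separate matter; 60 is used below because it is the plan's analysed number.

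**Variances per participant, general case.**
- Change score: s0² + s1² − 2·r·s0·s1
- ANCOVA: s1²(1 − r²)
- Difference between them: (s0 − r·s1)², which is never negative and is zero when r = s0/s1

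**Equal SDs (s0 = s1 = 1).** The change-score variance is 2(1 − r) and the ANCOVA variance is 1 − r², so the ratio is (1 − r²)/[2(1 − r)] = (1 + r)/2.

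**Power at 60 per group** (noncentral t, ignoring the one degree of freedom spent on the covariate). The standardised effects are:
- Reading A, 0.5 in SDs of the change: 0.5 for the t test, and 0.5/√[(1 + r)/2] for ANCOVA
- Reading B, 0.5 in SDs of the raw score: 0.5/√[2(1 − r)] for the t test, and 0.5/√(1 − r²) for ANCOVA

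| r | variance ratio | A: t test | A: ANCOVA | B: t test | B: ANCOVA |
|---|---|---|---|---|---|
| 0.3 | 0.65 | 77.5% | 92.1% | 63.1% | 81.3% |
| 0.5 | 0.75 | 77.5% | 88.0% | 77.5% | 88.0% |
| 0.7 | 0.85 | 77.5% | 83.8% | 93.9% | 96.7% |
| 0.9 | 0.95 | 77.5% | 79.6% | about 100% | about 100% |

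Under reading A, 80% power needs 64 per group with the t test, and 42, 49, 55 and 61 per group with ANCOVA at r = 0.3, 0.5, 0.7 and 0.9.

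**Unequal SDs, as an illustration.** Take s0 = 1 and s1 = 1.25.
- At r = 0.5: change score 1 + 1.5625 − 1.25 = 1.3125; ANCOVA 1.5625 × 0.75 = 1.1719; ratio 0.89 instead of 0.75.
- At r = 0.8 = s0/s1: change score 1 + 1.5625 − 2 = 0.5625; ANCOVA 1.5625 × 0.36 = 0.5625; ratio 1, so no gain.

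**The case against.** A two-sample t test on change from baseline is a legitimate analysis of a randomised trial, and it is the test on which section 2.8 sized the study. Using a different method for the secondary outcomes contradicts nothing. The size of the gain rests on an r that the article does not give and on equal SDs. At high r the gain is slight, and under the raw-score reading both analyses already have high power there. All of this stands, and it limits the point to one of efficiency and consistency.

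Three stronger readings are tempting, but the article does not support them.

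- *That the choice between t test and Wilcoxon inflates the type I error.* This would need the smaller p-value to be the one reported, which the plan does not say. The rule for choosing between the tests is detail that an article may leave to the full protocol or analysis plan.
- *That chance baseline imbalance biases the planned test.* Under randomisation such imbalance averages to zero. It is the source of the extra variance already counted above, not a further defect.
- *That the shortfall below 80% power makes this worse.* That shortfall comes from 60 against 64 per group and is a separate question. With 75 enrolled per group, 64 completers remain if dropout is at most 1 − 64/75 = 14.7%.

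A hospital covariate does not follow from the text either. Section 2.4 sends envelopes to each hospital but does not state that randomisation was stratified by hospital.

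**Conclusion.** The point holds as a matter of efficiency. The primary endpoint lacks the baseline adjustment that the plan gives to its other continuous outcomes, although the baseline score is collected from everyone. With equal SDs, ANCOVA cuts the variance by 35%, 25%, 15% and 5% at r = 0.3, 0.5, 0.7 and 0.9. In power at 60 per group, that is a gain of about 15 percentage points at r = 0.3 down to 2 at r = 0.9 if the effect size is in SDs of the change. In SDs of the raw score, it is about 18 points at r = 0.3 down to 3 at r = 0.7.

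That ANCOVA is in general at least as precise is secure. The magnitude is not, because it depends on r, on the ratio of the two SDs and on which SD the 0.5 refers to, and the article gives none of these. The change should be made, but the planned analysis is not invalid without it.

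**What to change.** In section 2.9, and in the matching sentence of the abstract, name one primary analysis: ANCOVA of the visit 3 awareness score on group, with baseline awareness as covariate, reporting the adjusted mean difference with its 95% confidence interval. This keeps the primary result on the scale of means, as the null hypothesis in section 2.8 requires. The endpoint need not be redefined, since regressing the change on group and baseline gives the same group effect. Keep the Wilcoxon test as a named sensitivity analysis only. Add hospital as a covariate only if randomisation was stratified by hospital.

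The cost is a sentence in each place. No new data, visits or participants are needed, and the method is already in the plan. The change should be fixed before outcome data are seen.

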## Discussion

3

This is a prospective, open-label, parallel group, randomized controlled trial aiming to evaluate the feasibility and effectiveness of a mobile application (MBBG) in managing subhealth statuses of healthy adults. One hundred fifty male or female subjects, without any specific diseases, will be allocated to either the MBBG or no-intervention group, with an allocation ratio of 1:1. Only the participants in the MBBG group will use the application for a total of 12 weeks. The awareness of subhealth status will be the variable primarily assessed, and changes to health promoting behaviors, QoL, TKM-based health questionnaires, and physical examination results will be also be statistically tested.

Mobile applications are a rising instrument aimed at helping people monitor their own health statuses, and in managing their own diseases, such as sleep disorders,^[18]^ diabetes,^[19]^ or even medication adherence.^[20]^ However, their effectiveness has not yet been confirmed.^[7]^ Also, no TKM-based application for health status monitoring, or subhealth management, exist. MBBG is the 1st mobile application, based on TKM theory as well as clinical research, that we expect will be feasible in the primary care for subhealth management.
